### Data management

Data management responsibilities for this study will be performed by the MRC/UVRI and
LSHTM Uganda Research Unit under the overall supervision of the research study data
manager. Study data will be managed electronically using REDCap (Research Electronic Data
Capture), a clinical data management system hosted at the MRC/UVRI and LSHTM Uganda
Research Unit. REDCap is a secure, web-based application that supports data capture for
research studies. This system will be used to create: (1) an intuitive interface for
validated data entry, (2) audit trails for tracking data manipulation and export
procedures, and (3) automatic data validation checks. Accruing data will be monitored
daily, and queries will be generated and shared with the research team by the study data
manager weekly. In addition, monthly data reports will be shared to monitor study
progress.

### Statistical considerations

Statistical analysis will be performed using STATA V.17 (StataCorp, Texas, USA). All
variables will be tabulated to assess distributions and to check for missingness and data
sparsity. Using descriptive statistics, categorical variables will be summarised as
frequencies and percentages. Continuous variables will be summarised as means and SDs or
medians and IQRs. Descriptive analysis will include key sociodemographic outcome
variables, for example, education level, socioeconomic status, baseline clinical
characteristics (age, sex, weight, BMI and waist circumference) and glycaemic control
characteristics (fasting glucose, 2-hour OGTT, HbA1c, fasting C peptide level).

Prevalence of diabetes will be computed as the number of diabetic cases at the end of the
study period as a proportion of the total number of participants enrolled into the study.
Similarly, prevalence estimates will be used to measure the burden of the different
vascular complications within this cohort. We will use Poisson regression analysis to
estimate the incidence rate of diabetes-related complications, including retinopathy,
nephropathy and neuropathy among individuals with diabetes and pre-diabetes. The
reproducibility of the diagnostic tests will be assessed by applying appropriate
diagnostic reproducibility statistics, including estimation of the dispersion of the data
values on index and repeat testing, interclass correlation and paired t-test (two tailed).
Furthermore, we will assess for percentage agreement using Bland-Altman’s methods
between the different tests. Before carrying out the analysis, test assumptions will be
checked. A two-sided p value of <0.05 will be considered a statistically
significant level for all analyses.

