#### Primary study outcome

Prevalence of diabetes and pre-diabetes.

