**Figure 1 F1:**
[figure not shown]
Participant’s flow. CGM, continuous glucose monitoring; DM, diabetes mellitus;
FPG, fasting plasma glucose; HbA1c, glycated haemoglobin; NGT, normal glucose
tolerance; OGTT, oral glucose tolerance test.

Study phases: this study will consist of overlapping phases, as described in table 2.

**Table 2 T2:** Implementation phases (I–IV)

Phase I	The first phase involves conducting the main baseline survey, whose outcomes are the prevalence of diabetes, pre-diabetes and associated risk factors, and glucose tolerance subgroups based on WHO criteria. This phase will include the following activities: Research team selection and training Stakeholder and community sensitisation Mobilisation and participant notification Recruitment of participants Obtaining consent and baseline questionnaire data collection Anthropometric measurements Baseline OGTT Blood and urine sample collection We will use systems already in place for the GPC cohort to achieve and maintain high levels of participation. These systems include: GPC census/survey teams, meeting the community advisory board, meeting local leaders, organising community meetings and participant notification.
Phase II	This phase involves the assessment of the reproducibility of the diagnostic approaches in a randomly selected set of participants. In this phase, we shall assess the diagnostic reproducibility of the fasting glucose and OGTT (diagnostic reproducibility substudy). We will determine whether participants with isolated impaired fasting glucose and isolated impaired glucose tolerance have elevated blood glucose in day-to-day living, compared with normoglycaemic individuals using continuous glucose monitoring. This phase will involve the following activities: Repeat OGTT Continuous glucose monitoring
Phase III	This phase aims to assess and describe any diabetes clusters or phenotypes by comparing baseline characteristics, and evaluating the distribution of various measures inclusive of biochemical parameters (eg, fasting and stimulated C peptide), adiposity and anthropometric indices. Further tests, including vascular complications assessment, endogenous insulin secretion measurement and islet autoantibodies profiles, will be done in future to better understand the differences between the various diabetes phenotypes.

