Phase IV	In this phase, we aim to establish well-characterised people with and without diabetes. The newly diagnosed participants with diabetes will be referred to the local diabetes clinics, where they will be managed according to the Uganda Ministry of Health guidelines. The newly diagnosed patients with diabetes and those with known diabetes will be followed up in clinics (supported by the research team) to study the *course of the condition*, including; (1) response to treatment: participants will be followed up at the clinic to assess glycaemic control (HbA1c) every 3 months, determine the time to treatment intensification (need for dosage increment, the addition of another drug or switching from oral hypoglycaemic agents to insulin), and (2) assess disease progression *through* (a) measuring of endogenous insulin secretion (using mixed meal tolerance tests), (b) assessment of insulin resistance and repeat vascular complications reassessment (including retinopathy, nephropathy). Concurrently, participants with pre-diabetes and those with normal glucose levels will be followed in a longitudinal study nested in the GPC to determine the incidence of diabetes.

GPC, general population cohort; HbA1c, glycated haemoglobin; OGTT, oral glucose
tolerance test.

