#### OGTT and biological sample collection

The OGTT will be performed following the WHO guidelines. The study nurse will confirm
if the participant fasted overnight for at least 8 hours. Baseline fasting blood
samples will be collected for fasting plasma glucose measurement and biobanking for
future diabetes and related studies. Following the collection of the fasting blood
samples, a standard 75 g of glucose will be administered, and a repeat blood
sample will be collected after 120 min. Participants who have not fasted
appropriately will be asked to return in a fasted state on another day.

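### The only stated formula for the primary diabetes prevalence counts cases at study end over everyone enrolled, which contradicts the protocol's own assignment of prevalence to the Phase I baseline survey

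*Protocol article*

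**What the plan says.** The primary outcome is "Prevalence of diabetes and pre-diabetes" (Primary study outcome). Two places say when it is measured, and they differ.

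- Table 2, Phase I: "The first phase involves conducting the main baseline survey, whose outcomes are the prevalence of diabetes, pre-diabetes and associated risk factors".
- Statistical considerations: prevalence of diabetes is "the number of diabetic cases at the end of the study period as a proportion of the total number of participants enrolled into the study".

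Table 2, Phase IV adds that participants with pre-diabetes or normal glucose will be "followed in a longitudinal study nested in the GPC to determine the incidence of diabetes". New cases are therefore expected after baseline, and they have their own measure.

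On testing, the section on OGTT and sample collection says: "Participants who have not fasted appropriately will be asked to return in a fasted state on another day". Under Definitions, any one of fasting glucose, 2-hour glucose, HbA1c or glucose-lowering treatment is enough to make a case. Statistical considerations says that variables will be checked for missingness.

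**The concern.** A baseline survey estimates the proportion who have diabetes when surveyed. The written formula moves the numerator to the end of a study that, as described, includes a follow-up phase, and it divides by everyone enrolled. Followed literally, it has two effects that pull in opposite directions:

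- People who develop diabetes during follow-up are counted as prevalent, although Phase IV counts them as incident. The result is neither a point prevalence at baseline nor a period prevalence over a defined interval. Enrolment runs from January 2022 to November 2023, so if the end of the study is a single calendar date, time at risk also differs between early and late enrollees.
- A person enrolled without any classifiable result can only sit in the denominator as a non-case.

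This is the only estimator stated for the outcome that the study is sized on. A confidence interval would not reveal either distortion, and more participants would not reduce it.

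**Working it through.** **Inputs from the protocol article.** Prevalence 5%, margin ±0.5 points, z = 1.96, response 80%, design effect 1.2 (Sample size determination); 8864 adults in the GPC villages and about 10 000 in Lukaya (Sample population). The incidence and the untested share are not given and are assumed below.

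**1. The plan's own figures.** n = z²p(1−p)/d² = 1.96² × 0.05 × 0.95 / 0.005² ≈ 7299, against the stated 7300. Then 7300/0.8 × 1.2 = 10 950, as stated. At 80% response, 0.8 × 10 950 = 8760 people are analysed, and the half-width is 1.96 × √(1.2 × 0.05 × 0.95 / 8760) = 0.50 points. The arithmetic reproduces, so ±0.5 points is the yardstick.

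**2. Untested people kept in the denominator.** If a share u of enrolled people is unclassified and none of their cases is detected, the formula gives 5% × (1 − u).

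| u (assumed) | Estimate | Error (points) |
|---|---|---|
| 5% | 4.75% | −0.25 |
| 10% | 4.50% | −0.50 |
| 20% | 4.00% | −1.00 |

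**3. Incident cases added to the numerator.** With annual incidence λ over one year in all people without diabetes and full ascertainment, the formula gives 5% + 95% × λ.

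| λ per year (assumed) | Estimate | Error (points) |
|---|---|---|
| 0.2% | 5.19% | +0.19 |
| 0.5% | 5.48% | +0.48 |
| 1.0% | 5.95% | +0.95 |

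The error reaches +0.50 at λ = 0.5/0.95 ≈ 0.53% per year.

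**4. Follow-up in the GPC only.** The GPC is the rural site: 8864/(8864 + 10 000) = 47% of invited adults. If only they are followed and recruitment is proportional (an assumption), the +0.50 in step 3 becomes 0.47 × 0.50 ≈ +0.24 points.

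**5. Both together.** With u = 10% and λ = 0.5%: (5% + 0.475%) × 0.9 = 4.93%. The two errors can nearly cancel, so a plausible-looking result would not show that the formula is sound.

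**6. Why the replacement denominator needs care.** Take 1000 enrolled, true prevalence 5%, and 100 people, missing at random, who have HbA1c only. Assume that HbA1c alone finds half of their 5 cases (a figure borrowed from the plan's assumption that OGTT doubles detection). Detected cases are 45 + 2.5 = 47.5.

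- Over all enrolled: 47.5/1000 = 4.75%.
- Over those tested positive on anything or fully tested negative: 47.5/(900 + 2.5) = 5.26%.
- Over the fully tested only: 45/900 = 5.00%.

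Keeping partly tested positives while dropping partly tested negatives biases the estimate upward. Requiring all three tests of everyone would instead exclude people who are already cases on one test.

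**The case against.** The fairest defence is that the sentence is loosely worded. The Abstract identifies cases by a population survey, Table 2 places prevalence in Phase I, and Phase IV gives later cases their own measure. The end of the study period may simply mean the end of the survey. That is a possible reading, but the text does not say so, and the study described includes Phase IV. The sentence needs correcting either way, and on that reading the denominator is unchanged.

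Several further objections stand and limit the point:

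- The one-year follow-up in the Abstract concerns the course of disease and response to therapy. People without diabetes are followed within the GPC, with no interval stated, so one year of incidence in all of them is an illustration only.
- The unclassified share may be small. HbA1c needs no fasting, treatment or HbA1c alone can make a case, unfasted people are asked back, and consent to all procedures is an eligibility condition (Ethics and dissemination). Consent is not completion, however, and someone with HbA1c only is missed if positive on glucose alone.
- Detailed missing-data rules are commonly left to an analysis plan. Their absence is not the point here; the point is a denominator that is stated.

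A reader might also infer that people who progress will deplete the pre-diabetes estimate, or that baseline cases who die or are lost will drop out of the numerator. The documents support neither: the formula names diabetes only, and nothing says that such cases are removed.

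**Conclusion.** The contradiction is certain: the analysis section fixes prevalence at study end over all enrolled, while Table 2 fixes it at the baseline survey and treats later cases as incidence. Because it affects the only stated estimator of the primary outcome, it should be corrected before analysis.

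The size cannot be determined from the documents. At 5% prevalence, either effect alone would equal the planned ±0.5-point margin under specific assumptions: 10% of enrolled people unclassified and undetected, or about 0.53% annual incidence over one year in everyone without diabetes. A reader might infer that the study will in fact report a prevalence biased by that much. That goes too far: both inputs are assumed, follow-up may cover only about 47% of invited adults, the two effects oppose each other, and the investigators may intend a baseline estimate. The sample size calculation is not affected.

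**What to change.** Replace the sentence under Statistical considerations with a definition that says:

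- **Numerator:** participants who meet the case definition (any one criterion, or treatment) at the Phase I baseline survey.
- **Denominator:** participants whose baseline status can be classified, meaning any positive criterion or treatment, or complete negative tests. People on diabetes treatment, who do not undergo OGTT, are then included.
- **Reporting:** the number enrolled but not classifiable, with a sensitivity analysis for partly tested people because of the upward bias shown in step 6. The method can be left to the analysis plan.
- **Pre-diabetes:** the same baseline time point.
- **Later cases:** reported only as incidence.

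The cost is a short rewrite and one sensitivity analysis. No new data are needed, the required sample size stays the same, and the analysed denominator falls only by the number who cannot be classified.

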**Participants:**

The study intends to enrol up to 11 700 individuals aged 18 years and above,
residing within the study area and not pregnant or within 6 months post-delivery
date. All participants will have detailed biophysical and biochemical/metabolic
measurements. Individuals identified to have diabetes and a random selection of controls
will have repeat tests to test reproducibility before referral and enrolment into a
diabetic clinic. Participants will then be followed up for 1 year to assess the
course of the disease, including response to therapy and diabetes-related
complications.

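### The Abstract and Table 2 disagree on who is retested for reproducibility, and if index-positive cases are included a pooled paired t-test will tend to report a fall when nothing has changed

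*Protocol article*

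**What the plan says.** Two places describe who is retested.

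- Abstract, Participants: "Individuals identified to have diabetes and a random selection of controls will have repeat tests to test reproducibility", before referral to a diabetic clinic.
- Table 2, Phase II: "This phase involves the assessment of the reproducibility of the diagnostic approaches in a randomly selected set of participants". The tests named there are fasting glucose and the OGTT.

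The Statistical considerations section does not choose between them. It promises "diagnostic reproducibility statistics, including estimation of the dispersion of the data" "values on index and repeat testing, interclass correlation and paired t-test (two tailed". It then says "we will assess for percentage agreement using" Bland-Altman methods, but words this as a comparison between the different tests. The significance rule covers every analysis: "A two-sided p value of <0.05 will be considered a statistically" significant level. Nothing is said about selection on the index value, or about whether cases and controls are analysed separately.

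**The concern.** The two samples differ in a way that matters for the named test. A random set is drawn without regard to the first result. A case group is drawn partly because the first result was high. Within-person variation then makes the second result lower on average, even if the test is perfectly stable. A paired t-test on pooled index and repeat values reads that fall as a change. The correlation also takes a value that depends on how many cases are mixed with how many controls, so it does not describe the surveyed population.

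The Introduction argues that OGTT glucose can be falsely raised after a missed or small evening meal. A fall on repeat OGTT caused only by selection would look like support for that argument.

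Two further points apply whichever sample is used. A paired t-test looks only at the mean difference, so large changes in both directions can cancel and leave it non-significant. And no index-versus-repeat measure of whether the diagnosis itself repeats is clearly named.

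**Working it through.** **The plan's own figure.** The only sample size given is for prevalence: 1.96² × 0.05 × 0.95 / 0.005² = 7299, which the plan rounds to 7300; 7300 / 0.8 × 1.2 = 10 950. Both reproduce. No number, SD or index-repeat correlation is given for the reproducibility substudy, so the inputs below are assumptions shown over a range.

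**Model on a standardised scale.** Index and repeat values are bivariate normal with correlation ρ and no true shift. Index-positives are the top 5%, the prevalence assumed in the sample size section. The cut-off is 1.645. The mean index value is φ(1.645)/0.05 = 2.063 SD in positives and −φ(1.645)/0.95 = −0.109 SD in negatives. The expected repeat-minus-index change is −(1−ρ) × the group's mean index value.

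| ρ | Positives only | 1:1 cases and negative controls | Random set |
|---|---|---|---|
| 0.7 | −0.62 SD | −0.29 SD | 0 |
| 0.8 | −0.41 SD | −0.20 SD | 0 |
| 0.9 | −0.21 SD | −0.10 SD | 0 |

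The 1:1 column is −(1−ρ) × (2.063 − 0.109)/2. Weighted back to the population the shift cancels: 0.05 × 2.063 − 0.95 × 0.1086 = 0.

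**Rejection by the two-sided 0.05 paired t-test with no true change (2000 simulated replicates).**
- Random set, as in Phase II: 4.4% to 5.6% for every ρ from 0.5 to 0.95 and every n from 20 to 365.
- 1:1 mix, total n = 100: 96%, 86% and 57% for ρ = 0.7, 0.8 and 0.9.
- Cases only, qualifying on any of three correlated tests, with one test analysed: shift −0.22, −0.15 and −0.08 SD; rejection about 75%, 60% and 37% at n = 100.

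**Glucose scale.** Assume true 2-hour glucose is exp(N(ln 6.3, SD 0.27)), with independent log-errors of SD 0.10, 0.15 or 0.20 at each visit and cases selected on 2-hour glucose ≥11.1 mmol/L. The mean change in a 1:1 mix is −0.43, −0.82 and −1.21 mmol/L. At total n = 100, t runs from about −3.1 to −4.5 across that range.

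**Correlation in the same simulation.**

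| Log-error SD | Whole population | 1:1 mix | Positives only |
|---|---|---|---|
| 0.10 | 0.87 | 0.91 | 0.56 |
| 0.15 | 0.76 | 0.81 | 0.40 |
| 0.20 | 0.63 | 0.69 | 0.31 |

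On the standardised scale at ρ = 0.8, the absolute-agreement intraclass correlation is about 0.80 in a random set, 0.85 in the 1:1 mix and 0.29 in positives only.

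**The case against.** Much can be said for the plan.

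- A reader might infer that reproducibility will be judged by the t-test. The text does not say so. The test is one item in an open list, beside dispersion and a correlation, and no sentence makes a non-significant result the criterion. This stands.
- A reader might model index-positives alone and quote a fall of 0.9 to 2.6 mmol/L. Neither place describes that sample: the Abstract adds random controls. Under the Definitions section a case may also qualify on fasting glucose, HbA1c or treatment, and the Introduction says known treated patients do not have an OGTT. Many cases are therefore not selected on the value being compared. This stands and shrinks the effect, but does not remove it.
- A reader might say that enrichment always inflates the correlation. It rises modestly in a mix of cases and controls and falls sharply in positives alone. What holds is that it depends on the sample.
- Under the Phase II wording regression to the mean does not arise at all. This stands, so that part of the point is conditional on the Abstract's version.
- *Interclass* is very plausibly a slip for *intraclass*. Agreed; it needs correcting and carries little weight here.
- The participant-flow figure is not available and may state who is retested. Detailed estimators belong in a fuller document, and reproducibility is not a listed objective or outcome. These limit the weight of the point. They do not reconcile two statements in the text that differ.

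**Conclusion.** The point holds in a conditional form. The Abstract and Table 2 conflict on the retested sample, and the analysis section applies a paired t-test without settling which is meant. With a random set the test keeps its level. With cases included because of a high index result and pooled with controls, it is likely to declare a fall when nothing has changed.

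The direction follows from the selection. The size depends on assumed within-person variation, case-control ratio, number retested and how cases qualified. At 1:1 with selection on 2-hour glucose it is about 0.4 to 1.2 mmol/L, and less if cases qualify on any test. The documents do not support saying that the analysis will mislabel the OGTT or fasting glucose, because one of the two stated designs avoids the problem.

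Separately from the sampling question, a non-significant t-test does not show reproducibility, and the agreement analysis is worded only as between different tests. The change is worth making. It does not touch the primary prevalence estimate.

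**What to change.** 1. Make the Abstract and Table 2 state the same retested sample, and name it in Statistical considerations.
2. If cases are included, analyse cases and random controls separately, or weight back to the surveyed population using the fractions retested in each group.
3. Limit any test of mean shift to participants not selected on their index result. Do not read a fall among cases as a real shift, or a non-significant test as evidence of reproducibility.
4. Replace *interclass* correlation with an absolute-agreement intraclass correlation, and report it with the within-person CV.
5. State limits of agreement for index versus repeat as well as between tests, and report the proportion reclassified (or kappa), with confidence intervals.

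The cost is revised wording and a little more analysis, with no added tests. Weighting back needs a record of how many controls were drawn and from whom. A new stratified sampling scheme is not needed, which matters because enrolment began in January 2022.

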**Methods:**

This research aims to (1) determine the prevalence and risk factors of diabetes in a
rural Ugandan population, (2) use clinical and biochemical markers to define different
diabetes phenotypes and (3) study the progression of diabetes in this population. We
will also assess the utility of the widely used tests (glycated haemoglobin (HbA1c),
oral glucose tolerance test (OGTT) and fasting glucose) in diagnosing diabetes.

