## Introduction

Diabetes is a global problem disproportionately affecting low-income and middle-income
countries (LMICs). According to the 2021 International Diabetes Federation estimates,
80% of the approximately 537 million adults (20–79 years) living with
diabetes reside in LMICs.^1^ In sub-Saharan Africa
(SSA), an estimated 24 million people are living with diabetes, which is projected to
reach 55 million within 20 years.^1^ Moreover,
the region is said to harbour the highest proportion of undiagnosed patients with
diabetes.^1^ This poses a major threat to sustained
development in the region if resources have to be found to treat the complications of this
condition.

An effective response will require a clear understanding of the burden, important local
determinants of risk, and pathophysiological and clinical manifestations of diabetes.
However, there are limited Africa data, with most coming from relatively small studies using
unstandardised methodologies. This may explain the significant variation in diabetes
prevalence observed between countries.^2^ Moreover,
there are concerns that some of the widely used tests to diagnose and monitor diabetes may
be unreliable in Africa. Although still a relatively unexplored area, the clinical utility
of glycated haemoglobin (HbA1c) in SSA has been questioned due to the high prevalence of
haemoglobinopathies such as sickle cell trait and other medical conditions that might affect
test reliability, including anaemia, malaria and HIV infections.^3–6^ Similarly, there are concerns about the utility of
oral glucose tolerance test (OGTT), the current gold-standard test for diagnosing
diabetes.^7^ It is not only complex and expensive but
may have other important limitations, such as the need to have adequate caloric intake in
the days preceding the test. Our preliminary study showed that a missed or small meal the
night before a test could lead to falsely elevated glucose.^8^ This might explain why some Africa studies have found a high prevalence of
diabetes or glucose intolerance where OGTT has been used. Therefore, OGTTs cannot be fully
relied on to screen for diabetes in settings where food insecurity or missed evening meals
are common.

There is also increasing evidence that diabetes may manifest differently in Africa compared
with its presentation in high-income countries. For example, while traditionally, type 2
diabetes is considered a disease of old age associated with obesity and insulin resistance,

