this condition appears to occur in relatively young and lean individuals in Africa and other
LMICs. This evidence initially came from Southeast Asia, where people were observed to
develop type 2 diabetes at lower levels of obesity than white Caucasians; this has led to
Asia-specific lower body mass index (BMI) thresholds for defining obesity.^9^ The explanation has been that Southeast Asians have a
propensity towards central obesity (and therefore insulin resistance) at relatively low body
weight. Our group recently showed that 50% and nearly 40% of newly diagnosed
type 2 diabetes (negative for pancreatic autoantibodies) in Uganda are younger than 50 years
and have a BMI of ≤25 kg/m^2^, respectively.^10^ In contrast to observations in Southeast Asia, the
‘thin’ patients showed no evidence of excess ectopic or visceral fat (using
anthropometric and electric bioimpedance measurements) or insulin resistance. Instead, they
had features consistent with insulin deficiency (lower fasting insulin, C peptide
insulinogenic index and Homeostatic Model Assessment for Insulin Resistance (HOMA-IR)).^11^

These observations raise important research questions and have huge potential clinical
implications: what are the mechanisms that drive diabetes in Africa; what are the right
approaches to its prevention and management? For example, are the lifestyle
interventions targeting weight loss or metformin use (as an insulin sensitiser), two
traditionally recommended first-line management options for type 2 diabetes, effective in
Africa?

This necessitates rigorous studies to unravel the complex manifestations of diabetes in
Africa and identify the right approaches to prevention and management. Therefore, in the
Diabetes in low-resource Populations Study, we aim to: (1) determine the prevalence of
diabetes in Uganda, (2) identify and characterise the different diabetes phenotypes, and (3)
develop a cohort in which we can examine and understand the course or progression of this
disorder and its different diabetes phenotypes. All patients except those with a known
diagnosis of diabetes (on oral or insulin treatment for diabetes) will undergo OGTT. With
this approach, we will be able to compare the diagnostic accuracy of fasting glucose and
HbA1c with OGTT.

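### The plan assigns Bland-Altman percentage agreement to comparison between different diagnostic tests, where Bland-Altman does not apply and does not yield percentage agreement

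*Protocol article*

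**What the plan says.** The Methods part of the abstract undertakes to assess the usefulness of HbA1c, "oral glucose tolerance test (OGTT) and fasting glucose) in diagnosing diabetes". The Introduction calls the OGTT "the current gold-standard test for diagnosing" diabetes. It adds that, because everyone except those already on treatment has an OGTT, "we will be able to compare the diagnostic accuracy of fasting glucose and HbA1c with OGTT".

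Statistical considerations then gives two consecutive sentences on test performance:

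- The first covers reproducibility and lists the dispersion of the "values on index and repeat testing, interclass correlation and paired t-test (two tailed").
- The second, introduced as a further analysis, says "we will assess for percentage agreement using Bland-Altman’s methods between the different tests".

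The Definitions section gives each test its own scale or cut-off. Diabetes is fasting glucose of at least 7.0 mmol/L, 2-hour glucose of at least 11.1 mmol/L, or HbA1c of at least 48 mmol/mol (6.5%). The lower limits for pre-diabetes are 5.6 mmol/L, 7.8 mmol/L and 42 mmol/mol (6.0%).

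**The concern.** A Bland-Altman analysis subtracts one measurement from another and describes the differences by their mean and limits. This answers a question about interchangeability, so both measurements must estimate the same quantity on the same scale. Fasting and 2-hour glucose share a unit but are different physiological quantities. HbA1c differs from both in quantity and in unit. The sentence also pairs this continuous-data method with percentage agreement, which is ordinarily a measure for categories, so it cannot be carried out literally.

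What is at stake is the assessment of test usefulness, which the Introduction motivates at length and on which the Discussion expects the data to bear. If the sentence is followed, a difference between tests would be reported as poor agreement even where they classify every participant identically.

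**Working it through.** **The article's own calculated figure.** The only computed figure is the sample size, n = z²p(1-p)/d². With z = 1.96, p = 0.05 and d = 0.005, n = 3.8416 × 0.0475 / 0.000025 = 7299, which matches the stated 7300. Inflation gives (7300/0.8) × 1.2 = 10 950, also as stated. The present point does not touch either number.

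**Inputs.** The cut-offs are those in Definitions. At a pair of cut-offs the two tests give the same classification, so a valid measure of diagnostic disagreement should show none there.

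**Difference a - b, and percentage difference 200(a - b)/(a + b).** The percentage form is included in case percentage agreement was meant as a percentage-scale Bland-Altman analysis.

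| Pair | Cut-off | a - b | Percentage difference |
|---|---|---|---|
| 2-hour vs fasting glucose | diabetes | 11.1 - 7.0 = 4.1 mmol/L | 200 × 4.1/18.1 = 45% |
| 2-hour vs fasting glucose | pre-diabetes | 7.8 - 5.6 = 2.2 mmol/L | 200 × 2.2/13.4 = 33% |
| HbA1c (mmol/mol) vs fasting glucose | diabetes | 48 - 7.0 = +41 | 200 × 41/55 = +149% |
| HbA1c (%) vs fasting glucose | diabetes | 6.5 - 7.0 = -0.5 | 200 × (-0.5)/13.5 = -7% |

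The glucose difference changes from 2.2 to 4.1 mmol/L between the two pairs of cut-offs, so subtracting a constant bias would not repair it. The HbA1c differences have no unit, and their sign depends on how HbA1c is reported. The percentage scale removes neither problem.

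**Illustration with perfect classification.** Let fasting glucose be an exact straight-line function of 2-hour glucose g through both pairs of cut-offs:

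- Slope = (7.0 - 5.6)/(11.1 - 7.8) = 0.424.
- Fasting = 5.6 + 0.424(g - 7.8).
- Difference = 0.576g - 2.29.

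Sensitivity and specificity against the 2-hour cut-off are then both 100%. Assume g is log-normal with median 5.9 mmol/L and log SD 0.38. These values are assumptions, not figures from the article; they put 4.8% of people at or above 11.1 mmol/L. A simulation of 200 000 people gave a Bland-Altman bias of 1.36 mmol/L and limits of -1.46 to 4.17 mmol/L, with the difference rising steadily with the mean. The bias and limits depend on the assumed distribution. That they can look poor for a perfect classifier does not.

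**The case against.** The strongest reply is that the sentence does not name the three tests. It follows the reproducibility sentence, and the Phase II substudy in Table 2 concerns repeat testing of fasting glucose and OGTT. If index versus repeat values of each test were meant, Bland-Altman would be valid. This stands to the extent that the reading is contextual. But the words are between the different tests, the index-repeat comparison has just been given its own methods, and the abstract and Introduction say which tests are to be compared. On the charitable reading the sentence still needs correcting.

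Some stronger conclusions might be inferred, and the article does not support them:

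- *The promised accuracy analysis cannot be delivered.* This would rest on silence. The article condenses a fuller protocol, and an analysis plan not shown may specify sensitivity and specificity. Their absence is not the point; the method that is stated is.
- *High agreement would be reported for a useless test.* At the 5% planning prevalence, a test that finds nobody agrees with the reference in 1 - 0.05 = 95% of people. The arithmetic is right, but the article sets out no categorical analysis against a reference. The 5% also describes the whole survey, not the repeat-test sample, which the abstract describes as people with diabetes plus random controls. The example is a reason to choose a better index in the fix, and no more.
- *Fasting glucose is judged against itself.* The fasting sample is drawn at the OGTT visit, but the abstract's Design paragraph lists fasting glucose and OGTT separately, and Definitions and Statistical considerations list the 2-hour value separately. The article leans towards the 2-hour value as reference and needs only to say so.
- *The data are already in hand.* Study status gives an enrolment start and an anticipated end. It does not say that collection is complete.

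A further caution is fair: the Introduction itself says that a missed meal can falsely raise OGTT results. Accuracy against the OGTT is therefore accuracy against an imperfect standard, though it is the comparator the article chose.

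**Conclusion.** The point holds as a defect in a stated method. Taken as written, and read with the abstract and Introduction, the sentence applies Bland-Altman to quantities that are not interchangeable and attributes to it a measure it does not produce. At the article's own diabetes cut-offs the spurious difference is 4.1 mmol/L between the two glucose values, and +41 or -0.5 between HbA1c and fasting glucose. The conclusion assumes that the different tests are fasting glucose, OGTT and HbA1c. If repeat values of a single test were intended, the fault is one of wording alone.

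Severity is moderate. Test comparison is a stated purpose but is neither the primary objective nor among the listed secondary objectives and outcomes. The prevalence estimate and the sample size are unaffected.

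**What to change.** 1. Restrict Bland-Altman to index versus repeat values of the same test, describe its output as bias and limits of agreement, and delete percentage agreement from that sentence.
2. For comparison between tests, cross-classify fasting glucose and HbA1c against the 2-hour OGTT value at the cut-offs in Definitions, among participants who undergo OGTT. Report sensitivity, specificity and ROC area with 95% CIs.
3. If an agreement index is wanted, use kappa or positive and negative agreement instead of raw percentage agreement.
4. State that the OGTT reference is the 2-hour value, so that fasting glucose is not part of its own reference standard.

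The cost is wording and analysis code. Every measurement needed is already scheduled in the protocol, and no change to recruitment, visits or sample size follows.
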